## Abstract

**Background:**

Sexual assault (SA) is a serious problem at universities. It is estimated that 1 in 5 women students will experience SA before they graduate.

**Objective:**

The primary aim of this randomized controlled trial is to test whether a synchronous web-based facilitated adaptation of an efficacious intervention (the Enhanced Assess, Acknowledge, Act [EAAA] program) can reduce the 1-year incidence of rape among first- and second-year undergraduate women. Secondary aims will assess the impact of the Internet-Delivered EAAA (IDEA^3^) on other forms of SA (attempted rape, attempted and completed coercion, and nonconsensual sexual contact). Tertiary aims will evaluate effects of the program on (1) survivor self-blame in the event of an assault, (2) 6 known mediators of the intervention effect to guide revision of IDEA^3^ if necessary, and (3) 2 exploratory outcomes measuring acceptance of sexualized aggression and sexual empowerment.

**Methods:**

In this multisite open-label randomized controlled trial, 1920 diverse women students at 2 Canadian and 4 US universities will be randomly assigned to receive either the 12-hour IDEA^3^ (intervention arm) or standard of care (control arm: 60-minute, web-based, live-facilitated consent workshop). Outcomes are measured at baseline, 1 week, 6 months, and 12 months post intervention. SA will be assessed using the Sexual Experiences Survey-Short Form Version. Survivor self-blame and outcomes known to be mediators of EAAA’s reductions in SA will also be measured.

**Results:**

Funding was received in October 2022. Recruitment began on October 2, 2023, and the first participant was randomized on October 23, 2023. As of August 2025, a total of 683 participants have been enrolled and randomized. Data collection will end in May 2027.

**Conclusions:**

If efficacious, IDEA^3^ will be made available to universities in Canada and the United States. To date, 6 provinces in Canada and the Campus SaVE Act in the United States require institutions to provide SA prevention programming. An evidence-based, cost-effective option that can be delivered remotely via the internet has the potential to become the gold standard. The research, therefore, has the potential to impact women’s health and safety internationally.

**Trial Registration:**

ClinicalTrials.gov NCT06058455, https://clinicaltrials.gov/study/NCT06058455

**International Registered Report Identifier (IRRID):**

DERR1-10.2196/72087

## Introduction

An estimated 1 in 5 undergraduate women experience sexual assault (SA) before graduation, driving depression, anxiety, and negative educational outcomes in survivors [1-3]. Unfortunately, few interventions designed for college students have been proven effective in reducing perpetration or victimization [4]. The Enhanced Assess, Acknowledge, Act (EAAA) SA resistance program is the only intervention proven in a randomized controlled trial (RCT) to reduce SA victimization and sustain these benefits beyond 6 months [4]. Compared with participants in the control arm of the trial, attempted and completed rape was reduced by 50% in female undergraduates who took EAAA, with effects lasting at least 2 years [5]. An implementation effectiveness trial of female-identified students at 5 implementing universities replicated the reductions in completed rape and all mediators for students beyond the first year in a more diverse sample [6]. The program also appears to have effects that generalize to reduce nonsexual intimate partner violence by over 50% for at least 12 months [7].

The EAAA SA resistance program consists of four 3-hour units led by 2 trained near-peer facilitators with a group of up to 20 women [8]. The program uses games, mini-lectures, facilitated discussion, and application and practice activities to facilitate knowledge and skill acquisition. Unit 1 (assess) focuses on improving women’s assessment of risk for SA involving male acquaintances and developing problem-solving strategies to reduce perpetrator advantages. Unit 2 (acknowledge) assists women in acknowledging the inherent danger in situations that have become coercive and exploring ways to overcome emotional barriers to resisting known men. Unit 3 (act) offers instruction and practice of various effective resistance options, focusing on common acquaintance SA situations. It also includes 2 hours of self-defense training based on Wen-Do Women’s Self-Defence, which teaches techniques designed to be successful against larger, stronger perpetrators. Unit 4 (relationships and sexuality) includes sex-positive sexual education adapted with permission from the Our Whole Lives program [9,10]. Activities build on what women have learned from the previous 3 units and apply this knowledge to longer-term romantic and sexual relationships. More detail is provided elsewhere [8,11].

Despite its efficacy and availability since June 2016, implementation of EAAA on campuses has been limited, with ongoing and new implementations interrupted during the COVID-19 pandemic. Interest has been high despite the absence of marketing efforts, and demand for training has been strong (15 trainings between 2016 and 2024 for 193 staff), with high satisfaction ratings. Nevertheless, relatively few universities send their staff for training, and the number of campuses implementing the EAAA intervention remains small. Some US administrators have expressed reticence due to the belief that a Canadian RCT is insufficient evidence of efficacy for US students. Resource issues have been an obstacle to the wider scale-up of EAAA despite institutional interest. Local implementation costs roughly US $232 per participant in the first year and US $200 in subsequent years [12]. Only 13 participants need to complete the program for one fewer attempted or completed rape to be experienced [5]. However, on campuses where resources are limited, this cost has been prohibitive. This estimate also does not include the cost and logistical burden of assigning an existing staff member as a Campus Trainer who must be trained and subsequently recruit, hire, train, and supervise a team of near-peer facilitators to offer the intervention on campus. Near-peer facilitators are often graduate students, which generates high turnover among facilitators if they are in 1- or 2-year master’s degree programs, and it can be difficult to recruit facilitators at undergraduate-focused institutions. Adapting EAAA for web-based delivery, which could be delivered to any campus by a centralized pool of peer facilitators, would eliminate the need to have trained staff locally. We estimate that this could reduce intervention costs to an institution by as much as 30%-40%.

In addition to reductions in cost and local implementation burden, a web-based version of EAAA offers key benefits for timing, fidelity, and accessibility of the intervention. Unlike in-person EAAA, students could more easily take the intervention remotely via web-conferencing before arriving on campus or in the preorientation “move in” week, addressing the issue that on many campuses, the highest-risk period for SA is in the first semester [13]. A centralized pool of full-time facilitators would likely enhance intervention fidelity over campus-specific facilitation models, as supervision quality of facilitators at a given institution may vary; further, small institutions where facilitators only offer 1 or 2 sessions per year may not be high enough frequency for facilitators to truly gain expertise with the intervention [14]. Centralization and web-based facilitation should therefore theoretically improve the effectiveness of the intervention across sites. A version of EAAA delivered via the internet would also increase the reach and coverage of the intervention to students at universities where intensive campus-run primary prevention programming is not offered due to a lack of institutional resources, which may disproportionately affect students who attend religious, rural, commuter, tribal, or small campuses.

Our adaptation of EAAA, called Internet-Delivered EAAA (IDEA^3^, pronounced “IDEA Cubed”), retains the synchronous, live-facilitated group learning format over videoconferencing and retains all of the core content of the theory- and evidence-based EAAA. We conducted a rigorous and systematic adaptation for internet delivery using the ADAPT-ITT framework [15]. This is a substantial innovation compared with existing web-based options, which are most commonly click-through or asynchronous trainings (eg, the popular sexual assault prevention for undergraduates training by Vector Solutions; formerly called Haven by Everfi). Asynchronous, individual web-based interventions have failed to reliably change even knowledge or attitudes about SA [16-18] or have had equivocal short-term effects on victimization [19]. Key advantages of the synchronous group format over individual click-through programs include learning from and with peers and peer facilitators, longer duration (at 12 hours) than other web-based programs, and the ability to address comments and questions that emerge from participants, allowing for meaningful integration of the material. Our 2-year adaptation process included extensive consultation with the University of Windsor’s Office of Open Learning staff with expertise in online education, pedagogy, and technology. A theatre test on a small number of first-year students (N=8) led to further revision followed by a single-arm pilot trial (N=65), which provided preliminary evidence of IDEA^3^’s feasibility, acceptability, and effects on the validated intermediary outcomes shown to mediate the effect of in-person EAAA on SA victimization [20]. The pilot study demonstrated the feasibility of the intervention, with strong recruitment and retention. The acceptability of the intervention was high, with participants reporting enjoyment (mean 8.2 out of 10) and willingness to recommend the training to others (mean 8.5 out of 10). Qualitative data from open-ended survey questions and focus groups indicated that within a short follow-up period, many participants had already used information and skills they learned in the program to detect coercive behavior and remove themselves from situations where they felt unsafe. Preliminary indicators of potential efficacy showed that the program increased self-defense self-efficacy and perceived risk of acquaintance rape while reducing acceptance of rape myths and beliefs about female participation in rape, echoing the changes found in these mediators of intervention effect in the in-person EAAA trial [21].

EAAA is part of a broader group of empowerment and resistance interventions developed in the field, but it has the strongest evidence base for efficacy in reducing victimization in North American university contexts. Other high-quality programs for university women had been developed since the late 1980s and were promising, but generally did not work to reduce victimization reliably for survivors or for the longer term [22]. A much longer empowerment self-defense program was found to be effective in reducing sexual violence in a propensity-matched quasi-experiment [23]. Unlike most other interventions in this space, EAAA is effective at reducing victimization in women with and without previous sexual victimization experiences [5,24]. EAAA was developed based on a decade of empirical evidence and theory [25] and, with pedagogical attention to the reality that survivors would always be present in the group, to address the difficult social and emotional context women face in society when the risk of SA is highest from people they should be able to trust (eg, male friends, intimate partners, and other acquaintances) in situations that should be safe (eg, parties, studying with classmates, and dating). EAAA is the only resistance program evaluated in North American universities with a rigorous RCT [4].

We focused on developing a web-based version of EAAA for scale-up, as it is the intervention with the strongest evidence base for yielding immediate, durable, and substantial reductions in assault victimization. While comprehensive prevention of sexual violence will involve ending perpetration and dismantling structural sexism, no existing interventions have been rigorously shown to durably reduce campus sexual violence perpetration, and a cultural shift is a long-term effort. In the meantime, EAAA prevents 1 attempted or completed rape for every 13 women who take the program, while reducing self-blame in the event of an assault [5,24]. An adaptation of EAAA for internet delivery would prevent imminent threats to safety and reduce sexual violence for women now and at scale, as work to end perpetration continues [26].

The next step is an RCT whose aim is to test whether IDEA^3^, when compared against a brief control workshop (“usual care,” ie, consent education), can deliver reductions in SA victimization of sufficient size to warrant scale-up to campuses in North America. Given that web-based interventions sometimes fail to produce benefits as strong as in-person ones [27], we have powered our trial to detect an intervention effect that is 80% as large as the effect size of in-person EAAA. We hypothesize that IDEA^3^ will reduce the 1-year incidence of completed rape by 37.75% (absolute difference of 3.7%) among first- and second-year undergraduate women in the United States, as compared with a consent workshop control condition. If successful, this trial of a web-based adaptation of the only intervention proven to prevent campus sexual violence and sustain those benefits in the longer term has the potential to revolutionize the fight against campus SA.

## Methods

### Study Design

This is a multisite, open-label, RCT.

### Inclusion and Exclusion Criteria

A total of 1920 first- and second-year undergraduate students will be enrolled in Canada and the United States. To be eligible, participants must (1) identify as women, (2) be between the ages of 17 and 24 years, (3) be first- or second-year undergraduate student, (4) be available during one of the intervention schedule blocks, (5) provide the contact information for another woman undergraduate who they would be willing to participate in the intervention with or express willingness to being partnered with another woman undergraduate at their university, (6) have access to internet and be willing to use the videoconferencing software ZoomPro (Zoom Video Communications, Inc) for the intervention, (7) provide informed consent, including to be recorded while participating, and (8) complete the baseline survey and be randomized with a partner who also meets all the criteria. At one site (University of Central Florida), participants must be 18-24 due to state law. Participants whose partners drop out within 24 hours of the first intervention session or do not show up for their assigned intervention after randomization will be permitted to participate alone. There are no exclusion criteria.

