### Recruitment

Recruitment began on October 2, 2023, at 4 sites: the Universities of Windsor and Guelph in Canada and the Universities of Michigan and Nebraska-Lincoln in the United States. In year 2 of the trial, recruitment was ended at the University of Nebraska and paused at the University of Michigan due to the departure of the site principal investigators (PIs) from those institutions. In year 3 of the trial, recruitment is planned at the University of Guelph, the University of Michigan, the University of Maryland, and the University of Central Florida. The 6 total sites represent diverse students, sizes, and contexts (eg, rural vs urban, proportion of students in residence, racial, and geographic diversity). Recruitment will only take place during the academic year when classes are in session. Multiple methods are used to attract participants to the study, including (1) recruitment emails through the registrar, faculties, or departments to all eligible students, (2) research participant pools, (3) social media ads or posts to relevant Facebook groups (eg, groups for students at a particular university), and (4) flyers will be distributed at on-campus events, posted in women’s bathrooms on campus, and sent digitally to student newsletters/newspapers, student organizations, or student-specific listserves at the sites of Universities. Not all recruitment methods will be used at all sites (eg, emails are permitted through the Registrar at certain sites but not others).

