#### Control Condition

Participant pairs assigned to the “usual care” control arm will receive one 60-minute session. The workshop focuses on (1) defining consent, including what components need to be present for consent to be meaningful, and (2) expanding the ways in which participants feel comfortable giving, refusing, and asking for consent. The control condition was selected to mimic what is currently available, “usual care” on typical college campuses, which is a brief consent workshop. The content is therefore based on the common components of consent workshops held at the study sites and community-based consent workshops (confirmed with participating campus materials and in consultation with the Ontario Coalition of Rape Crisis Centres).

As with the intervention arm condition, participants receive the consent workshop in pairs via Zoom in a private room (their own or provided to them on campus). These Zoom sessions include up to 8 pairs of participants (16 max) taking part in the workshop together. The control workshop is given by a well-trained RA. Participants who are assigned to the control arm will be informed of the importance of the control group to the study and their ongoing participation. They are made aware that they will be contacted in a year and offered the opportunity to take the full IDEA^3^ program.

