#### Between-Group Contamination

While our own and others’ research show that significant contamination is not likely to occur for an intervention of this length [49], as we have done previously, we will ask all participants at 1-week, 6- and 12-month follow-up the following questions: “Do you have any friends who were assigned to the other program in this study?” If the answer is “yes,” they are asked, “Did she/they share anything with you about what they learned in their program?” or “Did you share anything that you learned in your workshop with her/them?” depending on their group assignment. An open text box asks them to enter what was shared. We will describe the amount of contamination occurring and discuss its possible influence on the findings.

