## Results

This trial was funded in October 2022. Recruitment began on October 2, 2023. The first participant pair was randomized on October 23, 2023. A total of 683 participants had been enrolled in the ongoing trial by August 2025. Recruitment will end by May 2026, and data collection will end in May 2027. Results are expected to be published in 2028.

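### As written, eligibility admits women already trained in EAAA or IDEA3, or already randomized in this trial; the likely loss of power is small, but the rule should be closed

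*Protocol article*

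**What the plan says.** Under Inclusion and Exclusion Criteria, the protocol article gives eight numbered requirements and closes with "There are no exclusion criteria". On year of study, the requirement is to "be first- or second-year undergraduate student". Prescreening Survey turns away only women who decline to give demographic data or who fail the screening criteria. Partners have to meet the same criteria.

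Four other statements bear on this:

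- Introduction: EAAA has been available since June 2016, and the in-person trial found a benefit "with effects lasting at least 2 years". A single-arm pilot gave IDEA3 to 65 women.
- Recruitment and Results: "Recruitment began on October 2, 2023, at 4 sites", and "Recruitment will end by May 2026, and data collection will end in May 2027". Recruitment therefore spans three academic years.
- Control Condition: controls are told that "they will be contacted in a year and offered the opportunity to take the full IDEA^3^ program".
- Between-Group Contamination: the exposure question is "Do you have any friends who were assigned to the other program in this study". It concerns friends in the other arm, not the respondent's own earlier training. The items listed under Baseline Survey do not include prior EAAA or IDEA3 attendance either.

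**The concern.** An article may leave operational detail to the full protocol. This sentence is different, because it says affirmatively that nobody is excluded. A site applying it would have to accept a woman who has already had the intervention or its in-person parent.

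Such a woman weakens the comparison in either arm. As a control she is not a usual-care participant, because on the article's own account her protection outlasts the 12-month follow-up. In the IDEA3 arm she has less left to gain. Both effects shrink the expected difference. The trial is planned at 80% power, with nothing in reserve beyond the allowances for pairing and dropout.

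If a woman were randomized a second time, her second baseline would follow her first exposure. The planned variance inflation covers correlation within pairs, not two records from one person.

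**Working it through.** **Inputs** (Sample Size Considerations, with allocation from Randomization): control 9.8%, IDEA3 6.1%, two-sided 5%, power 80%, 1:1 allocation, design effect 1.031, loss to follow-up 10%.

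**Reproducing the plan.** The pooled-variance formula for two proportions is

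n per arm = [1.960·√(2·p̄·(1−p̄)) + 0.842·√(p1(1−p1) + p2(1−p2))]² / (p1−p2)²

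With p̄ = 0.0795, the two square roots are 0.3826 and 0.3817, so n = (0.7498 + 0.3212)² / 0.037² ≈ 837.9. That rounds up to 838 per arm, or 1676. Then 1676 × 1.031 / 0.90 = 1919.95, or 1920. Both stated figures reproduce.

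**Dilution.** Let f be the share of participants already trained, equal in both arms because training precedes randomization. Assume the worst case: they carry the full 6.1% risk whatever arm they enter, and repeat training adds nothing. The control incidence becomes 9.8 − 3.7f points, IDEA3 stays at 6.1%, and the difference is 3.7 × (1 − f). Power uses 838 per arm and the same formula.

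| f (assumed) | Control | Difference | Power | Enrolment for 80% power |
|---|---|---|---|---|
| 0 | 9.80% | 3.70 points | 80.0% | 1920 |
| 1% | 9.76% | 3.66 points | 79.3% | 1957 |
| 2% | 9.73% | 3.63 points | 78.6% | 1991 |
| 5% | 9.62% | 3.52 points | 76.3% | 2106 |

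Giving trained women the in-person rate of 5.2% instead hardly changes this: at f = 5%, power is 76.5%.

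**What share is plausible?** The article gives none, but some of its counts help:

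- If every pilot participant had enrolled, f would be 65/1920 = 3.4%.
- By August 2025, 683 women had been enrolled, so about 683/2 ≈ 342 had been assigned to IDEA3.
- For in-person EAAA, the Introduction says that few campuses run it.

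**Where could a first-year return as a second-year?**

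- Maryland and Central Florida are named only for year 3, so no earlier cohort is described there.
- Nebraska-Lincoln ended in year 2.
- Michigan was paused in year 2. With normal progression, its year-1 first-years are third-years when it resumes, and so ineligible.
- Windsor is not listed for year 3. It offers a route only from year 1 to year 2, and only if it recruited then.
- Guelph recruited from the start and is in the year-3 plan ("In year 3 of the trial, recruitment is planned at the University of Guelph, the University of Michigan"), so it is the main route.

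**Repeat records, if any.** Treating a second record as no new information, 1% repeats give 79.6% power, 2% give 79.2% and 5% give 78.0%.

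**The case against.** The strongest reply is that the target of 1920 students ordinarily means 1920 different people, and that blocking repeat sign-ups is a matter for the full protocol. The article describes a setting where repeats are easy to spot. Each woman has an individual camera-on interview with a facilitator, IDs are linked in REDCap, contact details are updated during follow-up, and session attendance is recorded. Someone returning within a year would still be under follow-up from her first enrolment. Controls have a promised route to IDEA3 without enrolling again, and it opens when a first-year control is at or near the end of her eligibility. Finally, any dilution acts toward no difference and cannot create a false positive.

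Most of this stands. A reader might infer that women are in fact being enrolled and counted twice. The article does not say so; it only fails to bar it. A reader might also infer that trained women would be invisible at analysis. That is not so for training within this trial, which attendance records can trace; only training outside it could go unrecorded. Nor do the counts support large losses of power. A share of 10% would mean 192 trained women, and 20% would mean 384, which is more than everyone assigned to IDEA3 by August 2025.

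What the reply does not remove is the explicit sentence. It closes the list of criteria, and women trained outside the trial meet that list without any described step to identify them.

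**Conclusion.** The point holds as a flaw in the stated eligibility rule with a probably small effect. Women with prior EAAA or IDEA3 training are eligible as written, and their inclusion would bias the comparison toward no difference. Re-randomization is permitted by the wording, over a narrow set of sites and years, but is not shown to occur. The power loss is about 0.7 percentage points at a 1% share, 1.4 at 2% and 3.7 at 5%. All of these shares are assumptions. The figures also assume fully retained benefit and no gain from repeat training, so they are upper limits for each share. The change is still worth making: it is cheap, it protects the usual-care contrast, and 1920 − 683 = 1237 women remained to be recruited as of August 2025.

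**What to change.** Replace the sentence on exclusion criteria with an exclusion for any woman who (a) has previously been randomized in this trial, or (b) has previously attended any session of EAAA or IDEA3, including the pilot. Apply it to both members of a pair, through one added prescreening question and a check against existing REDCap records. If staff already screen for this, correct the sentence so that it describes what is done.

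For women already enrolled, search REDCap for repeat randomizations. Only if any are found, analyse the first randomization.

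The cost is one screener item, a database check and a short amendment. The downside is the loss of a few sign-ups. The planned 1676 evaluable and 1920 enrolled do not change.
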